### Trial Intervention

The trial intervention aims to combine management strategies already familiar to primary care staff, but in a concerted and consistent manner [22]. It was found to be well within the expertise of the practice nurses involved in the feasibility study. The model is similar in some ways to that used in the longer-term care of patients with asthma or diabetes in primary care. Components include:

### Recall system

Recall systems have been set up within the participating practices based on the practice computer and managed by the practice research nurse, who is responsible for contacting the intervention patients. If participants fail to attend a review appointment they are asked to make another appointment. If they fail to attend again, they are contacted for review at the next time point.

### Clinical review

For all intervention participants the practice research nurse undertook a baseline assessment, asking about current mood, social circumstances, current treatment (medication and/or psychological therapy), and any side-effects or queries. Participants were given a specially written educational booklet about depression and its treatment at this initial appointment. There is evidence that appropriate patient education materials can be helpful as part of an integrated approach' [11-13]. This patient booklet was written specifically for the patients in this study and outlines current evidence based thinking about the treatment of depression.

The nurses answered participants' questions about current or past treatments and checked their concordance with the treatments they were currently receiving, clarifying any reasons for poor concordance. If there were current symptoms of depression, alternative or additional treatments were discussed. These could be pharmacological, psychological or social, with the rationale and evidence for any of these being made clear, both in the background literature given to patients and in their discussion with the nurses. Social factors, which could be contributing to the chronicity of patients' depression, were explored (e.g. social isolation, low physical activity, unemployment, finance, housing) and appropriate advice given or referrals to other agencies made. The importance of patient choice and active participation in this process and in the treatments selected was emphasised.

A joint management plan was then formulated between the nurses and each of their patients and reviewed during subsequent appointments, together with a review of how the patient was feeling and any progress made with previous goals set. We aimed to teach participants how to monitor their own mental state and to have a sense of possible predictors of relapse. Evidence from other studies indicates this can be helpful [15].

### Timing of intervention appointments

Intervention patients were seen for a baseline assessment, after one month and then two months later - i.e. three times over the initial 3 months of the study. The purpose of having the initial appointments more closely spaced was to allow sufficient time for the nurses to get to know the patient well and to formulate a clear management plan together. After this, the reviews for intervention patients took place 3 monthly for the remainder of the 24 month trial period, but could be more frequent if there were any significant clinical concerns about the patients' mood. Such a flexible approach was found helpful in a two-year study with good outcomes, and the arrangements were left to the discretion of the nurse [15]. If patients were keeping well, it was considered appropriate to conduct this review over the telephone, with evidence from other studies showing this to be feasible [23]. Nevertheless, we asked the nurses to have face-to-face contact with participants every few appointments. If nurses were concerned about a patient, they were asked to discuss them with the relevant GP, who might also see the patient if indicated.

### Treatment as usual

During the 24 month study period the participants in the control arm had 'treatment as usual' and continued to see their GP on request, with no restrictions placed on any interventions which the GP might recommend. It was stipulated that the control arm participants should not see the practice research nurse for any mental health intervention, although they might see her for physical health problems.

### Research nurse training sessions

The research team provided 4 full days training for all the participating practice nurses as follows:

• Day 1: covered the procedures required to recruit participants to the trial, checking their eligibility (including conducting the CIDI interview) and conducting the computerised randomisation.

• Day 2: covered the procedures and information required for the intervention appointments, including assessment of a patient's level of depression, details of evidence based pharmacological and psychological treatments for depression, and the importance of considering relevant social factors.

Brief training was given in problem solving techniques to help patients address some of these difficulties.

• Day 3: A further day's training was arranged after 6 months for the nurses to discuss some of their clinical cases, and in particular to focus on ways of working with their more complicated or resistant clients. Brief training was given in the use of simple motivational interviewing techniques to use with patients finding it difficult to make any changes in their lives [24].

All the information from the three training days was written in a manual for the nurses to take away with them, and they were regularly updated with information about potentially useful resources available. The nurses were also encouraged to ensure that they maintained access to up to date information about appropriate local voluntary and other organisations which they could encourage patients to contact where appropriate.

• Day 4: This training session was for the procedures required for the final assessment at 24 months, including conducting a further CIDI interview (see further details below).

### Clinical Supervision sessions

Each nurse was assigned a member of the research team as a 'clinical supervisor' (two of these were general practitioners with a special interest in mental health and one was a clinical psychologist). Nurses had regular telephone contact (generally every 3-4 months) with their supervisors throughout the trial period. The format used was a general review, giving nurses the opportunity to discuss their intervention cases and any concerns they might have, as well as the supervisor making suggestions about possible changes in approach or treatment where appropriate. Nurses could also contact their clinical supervisor in between if they had a particular concern or query about a patient.

### Outcome measures

**The primary outcome measure **is the Beck Depression Inventory (BDI-II). The BDI-II is a reliable and well-validated measure for measurement of the severity of depression and monitoring its clinical outcome, which has been used in many primary care studies [21]. It will also be involved in the assessment of cost-effectiveness as part of the health economic analysis.

### Secondary outcomes (table 1)

**Table 1 T1:** Frequency of measuring outcome measures

	BDI-II	WASAS	CIDI (24 months)	SAPAS	EQ-5D	CSRI	Service Data (24 months)
**Baseline**	√	√	√	√	√	√	√
**3 months***	√						
**6 months**	√						
**12 months**	√						
**18 months**	√						
**24 months**	√	√	√		√	√	√

* We had initially planned to collect BDI-II questionnaires 3 monthly, but decided this was too onerous for participants and risked a poor response rate, so this was altered to 6 monthly from the 6 months time-point

(a) Depression-Free Days: These will be assessed in two ways. They will be calculated using BDI-II assessment scores following the method of Lave et al. [25]. This will then be compared with patients' self-completed records of which days they felt they were significantly depressed, to see how a continuous form of data collection compares with a statistical method for assessing persistence of depression. (Our feasibility data indicates that patients will be prepared to keep such on-going records).

(b) Social Functioning: This will be measured using the Work and Social Activity Scale (WASAS). This is a well-established, brief questionnaire, which we will use to assess participants' difficulties with physical and social functioning associated with their depression [26]. It has been validated for use in primary care populations with depression.

(c) Frequency of Depressive Episodes: Will be collected using the CIDI questionnaire [20]. This instrument is frequently used in psychiatric epidemiological studies and has been modified to allow us to collect diagnostic data on trial participants as regards their depression using DSM-IV criteria for the 36 months before recruitment as well as the 24 months of the trial.

(d) Patient personality factors: Participants are asked at baseline to complete the Standardised Assessment of Personality - Abbreviated Scale (SAPAS), a brief measure of personality variables developed for use in primary care [27].

(e) Quality of life: This will be measured by the Euroquol EQ-5 D, which will generate scores for the cost-utility analysis [28].

(f) Resource use and costs: Data on all services used and productivity losses over a retrospective 3-month period will be collected using a modified version of the Client Service Receipt Inventory (CSRI), which has been used in numerous economic evaluations, including in primary care populations [29].

(g) Practice service data: The research nurses will also be asked to count the number of GP attendances and home visits, practice nurse contacts, referrals for psychological therapy and prescriptions for psychotropic medication for all participants for the 24 months before recruitment and the 24 months of the trial.

In order to maintain blindness the final research assessment will be carried out by a different person. This may be another nurse at the practice, a MRC GPRF regional training nurse or a Mental Health Research Network Clinical Studies Officer. All participants will be asked at the outset of the final assessment not to reveal their trial arm allocation. As a check on potential bias, each practitioner assessing outcome will be asked to record which trial arm they think each patient they have assessed was in, to see whether the probability of a correct 'guess' is greater than chance.

### Depression-free Days recorded in Mood Diaries

Following successful piloting in the feasibility study all participants were asked to complete regular mood diaries, indicating for each day whether they had been depressed or not. This was something that had been both feasible and acceptable for the six months of the pilot study, but proved overly time-consuming and onerous for many participants in the full trial, with the response rate being quite poor after the first 3 months.

We therefore reduced the requirement to completion of the diaries for 50% of the project time. An algorithm was constructed, with the 2 years of the trial follow-up divided into eight 3 month portions and participants randomly allocated to receiving the diaries for four of these time periods. Random allocation of diary periods means that data can be imputed for the whole trial period and used as a patient record of their depression free days, as well to validate the scores calculated using the BDI-II scores by the method of Lave et al. [25].

The questionnaires listed were self-completed, apart from the CIDI which was administered by the research nurses in the practices, who also collected the service usage data. In order to ensure good response rates, participants were given a booklet with all the self-completion questionnaires to fill in when they attended the surgery at baseline and at 24 months for their assessments.

BDI-II questionnaires and mood diaries during the intervening two years were posted to all participants with a self-addressed envelope enclosed for their reply. A reminder letter and copy of the questionnaire was sent after two weeks if participants did not respond. If they failed to return the primary outcome measure, the BDI-II, they were telephoned by the practice research nurse to prompt them to return the questionnaire.

### Proposed sample size

We conducted two sample size calculations - for both a 4 and 5 point difference in the primary outcome measure, the BDI-II. In order to detect a 4-point difference on the BDI-II (assuming a pooled standard deviation of 11.0) at 90% power and the 5% level of significance, the required sample size was 318. To meet the objectives of the economic analysis (see details below) data from a previous trial comparing GP care and talking therapies showed a sample size of approximately 200 in each study arm would be required, rising to 534 using an estimated 25% drop-out rate [30].

To take account of practice clustering we used an intra-class correlation (ICC) of 0.02 which, given an estimated 12 to 14 patients recruited per practice, inflated our sample size to 630 from 47 practices (see table 2 below). We considered this to be a suitable ICC given that a primary care trial with the BDI as the outcome for GPs using cognitive behavioural techniques with their patients gave an ICC of 0.13 [31].

**Table 2 T2:** Four Point Difference in BDI

ICC	Design effect*	Total sample size		Number of practices required
		Required	With 25% drop-out	
0	1	400	534	40
0.01	1.09	436	581	44
**0.02**	**1.18**	**472**	**630**	**47**
0.03	1.27	508	678	51
0.04	1.36	544	725	54
0.05	1.45	580	774	58

*Design effect = 1 + (n-1) × ICC, based on clusters with 10 individuals per cluster.

A 4 point difference in BDI score would be a conservative result and is the smallest difference we would expect to achieve. In a previous trial of counselling in primary care the results showed a 5 point difference in outcome which is equivalent to a clinically important treatment effect of 0.5 [31].

We therefore repeated the same calculations for a difference in outcome of 5 points on the BDI, which indicated that we would need 423 participants from as few as 32 practices recruiting 12 to 14 patients each. This would also provide sufficient power for a cost-effectiveness analysis using this outcome.

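### The planning ICC of 0.02 is justified by a cited trial whose ICC is 0.13, and the two figures must be reconciled

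*Protocol article*

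**What the plan says.** All of this is in the Protocol article, under Proposed sample size.

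- The clinical calculation takes a 4-point BDI-II difference and an SD of 11.0, and reports the result thus: "at 90% power and the 5% level of significance, the required sample size was 318".
- The economic calculation: "a sample size of approximately 200 in each study arm would be required, rising to 534 using an estimated 25% drop-out rate".
- The clustering allowance: "To take account of practice clustering we used an intra-class correlation (ICC) of 0.02". With 12 to 14 recruits expected from each practice, the authors report that this "inflated our sample size to 630 from 47 practices".
- The reason given for 0.02: it is described as suitable on the ground that a primary care trial with the BDI as outcome, "for GPs using cognitive behavioural techniques with their patients gave an ICC of 0.13".
- The footnote to Table 2: "Design effect = 1 + (n-1) × ICC, based on clusters with 10 individuals per cluster". The table covers ICCs from 0 to 0.05 and has the 0.02 row in bold.

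Elsewhere, the Feasibility Work, Methods/Design and Randomisation sections say that patients are randomised individually within practices and that a cluster-randomised design was not adopted.

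**The concern.** A cited ICC of 0.13 cannot be a reason for planning on 0.02. The text does not bridge the gap: it mentions no difference in clustering unit, no covariate adjustment and no other source. Table 2 is the plan's sensitivity range, yet it leaves out the only empirical value the plan cites.

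The chosen ICC selects the bold row: design effect 1.18, 472 required, 630 with drop-out, 47 practices. If 0.13 is right, the allowance for clustering has no stated basis. If it is wrong, the reader is given a false figure as the support. The article's Discussion also says that the 558 recruited should be enough to show a clinically significant effect, and a reader cannot judge that while the section holds two incompatible ICCs.

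**Working it through.** **Inputs.** From Proposed sample size: difference 4 points, SD 11.0, 5% significance (taken as two-sided, which reproduces the plan's figure), 25% drop-out, 10 per cluster, ICC 0.02 planned and 0.13 cited. From Interim results: 558 recruited in 42 practices. The 10 per cluster fits completers: 12 to 14 recruited × 0.75 = 9 to 10.5, and 558 × 0.75 / 42 = 9.96.

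**1. The plan's own figures.**
- Per arm: 2 × (1.96 + 1.2816)² × 11² / 4² = 158.9, so 159, and 318 in total. This agrees.
- Table 2 at ICC 0.02: 1 + 9 × 0.02 = 1.18; 400 × 1.18 = 472; 472 / 0.75 = 629.3, so 630. This agrees. The other rows reproduce to within one patient.
- Table 2 inflates 400 (the economic requirement), not 318. The stated 90% power belongs to 318 before clustering and drop-out.

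**2. The gap.** 0.13 / 0.02 = 6.5. The largest ICC in Table 2 is 0.05.

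**3. The plan's formula at ICC 0.13.** Design effect 1 + 9 × 0.13 = 2.17.
- On the Table 2 base: 400 × 2.17 = 868; / 0.75 = 1,158.
- On the 4-point, 90% power base: 318 × 2.17 = 690; / 0.75 gives 921 after rounding up.

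Power is Φ(4 / (11 × √(4 / Neff)) − 1.96), with Neff = completers / design effect:

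| Completers | ICC | Neff | Power |
|---|---|---|---|
| 472 (planned) | 0.02 | 400 | 95.3% |
| 472 (planned) | 0.13 | 217.5 | 76.5% |
| 418.5 (558 × 0.75) | 0.02 | 354.7 | 92.8% |
| 418.5 (558 × 0.75) | 0.13 | 192.9 | 71.4% |

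**4. Structures that fit randomisation within practices** (418.5 completers, ICC 0.13).
- *Outcomes cluster by nurse in the intervention arm only.* I assume equal arms, one nurse per practice and 5 to 7 intervention completers per nurse. The lower figure is about half of 9.96; the upper is half of 14. The design effect is the average over arms, [1 + 1 + (m − 1) × 0.13] / 2. With m = 5 it is 1.26, Neff 332, power 91.2%. With m = 7 it is 1.39, Neff 301, power 88.4%. At ICC 0.02 the same structure gives 95.4% and 95.1%.
- *Practice in the model, no treatment-by-practice effect.* Between-practice variance drops out of the comparison, so the SD becomes 11 × √(1 − 0.13) = 10.26, and power is 97.9%.

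**5. If 0.13 were a misprint.** Taking 0.013 purely as an illustration: design effect 1.117; 400 × 1.117 = 447; / 0.75 = 596; power 96.2% at 472 completers. In that case 0.02 would be on the cautious side.

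**The case against.** The strongest reply is that the power loss belongs to a design this trial does not have. The formula 1 + (n − 1) × ICC describes randomisation of whole practices. With patients allocated in blocks within each practice, and multi-level modelling planned under Planned analyses, most between-practice variance cancels, so using the formula was cautious with respect to a practice-level ICC. This stands, and it limits the size of the point.

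The cited ICC may also measure something else. The article does not say whether 0.13 is at GP or practice level. That is a fair reason for not calling 0.02 wrong, but the article does not offer it as the explanation.

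The plan regards 4 points as conservative. At 5 points, even the unsuitable formula with ICC 0.13 gives about 88% for 418.5 completers. Recruitment is also complete, so the planning ICC no longer sets any number, and clustering will be estimated from the data.

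A reader might infer that the stated 90% power falls to about 71%. The article does not support this, because the 90% belongs to 318 patients without clustering and the 71% to 558 recruits less 25%. Compared on the same number, the fall is 95.3% to 76.5%, or 92.8% to 71.4%, and only under the plan's formula.

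None of these replies repairs the sentence that offers 0.13 as support for 0.02.

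**Conclusion.** The contradiction stands: the only evidence given for an ICC of 0.02 is a value 6.5 times as large and outside the tabulated range. Either the cited figure is misprinted or the planning value lacks its only stated support. The article cannot decide between these, so a misprint should not be taken as established.

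The consequence for power is conditional. On the plan's own method, 0.13 would mean 4-point power of about 76% at the planned completers and about 71% at the recruited number with 25% loss. On structures that fit the randomisation, power for the recruited number is about 88% to 91% (nurse clustering in one arm, 5 to 7 completers per nurse) or about 98% (practice modelled, no treatment-by-practice effect). A reader might conclude that the trial is underpowered; these figures do not show that. All of them assume SD 11.0, a two-sided 5% test and 25% loss. The fault is in the stated justification for the sample size, not in the arithmetic of Table 2, which reproduces.

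**What to change.** Check the cited ICC against its source, including the level (GP or practice) at which it was estimated. The same reference number is also attached to a differently described counselling trial later in the section, so confirm which source gives the ICC.

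- If 0.13 is a misprint, correct it.
- If it is 0.13, remove the claim that it supports 0.02, and either give another basis for 0.02 or say that it is an assumption. Add a 0.13 row and restate power for the 558 recruited as a range over ICC 0.02 to 0.13, using a design effect that fits randomisation within practices.

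The cost is one sentence and one table row. No analysis changes, and the stated power may be slightly less favourable: with nurse clustering in the intervention arm, about 95% at ICC 0.02 against 88% to 91% at 0.13.

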## Feasibility Work

A 6-month pilot feasibility study was conducted in three general practices in North London, with 35 patients randomised by practice. The aim was to test out the intervention and the measures to be used in a full trial and to conduct qualitative, in-depth interviews with 12 patients who completed the intervention. Participants responded well to this practice nurse intervention, particularly valuing contact with someone who they perceived as a 'normal, mature person drawing on their own experience', rather than with a mental health professional. Practice nurses had more time than GPs, gave helpful, practical advice and a sense that they were interested in patients' problems [18].

This pilot study demonstrated that it was feasible to recruit sufficient eligible participants willing to take part and that they would be able to complete the relevant questionnaires. The feasibility study also indicated that the chances of contamination between intervention and control patients within a practice was low, as the majority of the patient contact in the intervention was carried out by nurses who were very unlikely have consultations with the control patients to discuss their mental health symptoms, although they might carry out other practice nurse consultations for physical health reasons. We therefore decided to randomise by patient within practices in the main trial, rather than carrying out a cluster randomisation design.

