### Randomisation

We used the MRC computerised telephone randomisation service in Aberdeen, which provides an efficient automated 24-hour service and the choice of randomisation by telephone or Internet in each case. Randomisation was at the patient level within each practice, using a block design to maintain a balance of numbers in the control and intervention groups.

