### Planned analyses

All data will be double entered, using a reputable data entering service, blind as to participant group.

A description of baseline characteristics will be made between those randomised to the control and intervention groups.

All outcome analyses will include individuals in their randomised arm (intention to treat). Initial descriptive statistics will be used to summarise the differences in outcome between the two groups. We will present means and standard deviations for normally distributed, continuous variables and medians, with inter-quartile ranges, for those not normally distributed. Categorical outcomes will be presented as frequencies and percentages within each of the categories.

Observations at each time point on the same individual will not be independent so a repeated measures generalised linear model approach will be used [32]. This will also allow adjustments to be made for the natural clustering inherent in the study design. Continuous outcomes, which are measured at baseline and at the end of follow-up, will be analysed using analysis of covariance (ANCOVA) to adjust for any differences in baseline values [33]. Results will be presented as adjusted differences in means with 95% confidence intervals and associated p-values. Categorical outcomes will be compared using logistic regression and summarised by comparing the group values of the odds ratios for each outcome using 95% confidence intervals and associated p-values. Statistical techniques will be used to assess the impact of potential missing data [34]. Multiple imputation using a predictive model based approach will be used to impute missing values [35]. No interim or sub-group analyses are planned.

The impact of clustering by GP and/or nurse will be investigated using multi-level modelling. This will ensure that estimated standard errors of the treatment effect will be adjusted for the cluster effects.

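### Table 2 inflates the sample size with the design effect for randomising whole practices, although patients are randomised within practices, so 472/630 is not the requirement for this design

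*Protocol article*

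**What the plan says.** The article is clear about the unit of randomisation. Under Feasibility Work it says: "We therefore decided to randomise by patient within practices in the main trial, rather than carrying out a cluster randomisation design". The Randomisation section repeats it: "Randomisation was at the patient level within each practice, using a block design to maintain a balance of numbers in the control and intervention groups". The opening of Methods/Design says the same.

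The Proposed sample size section starts from a 4-point BDI-II difference, "assuming a pooled standard deviation of 11.0", and reports that "at 90% power and the 5% level of significance, the required sample size was 318". It then moves to about 200 per arm (400 in total) for the economic objective, or 534 with 25% drop-out. It inflates 400 for practice clustering at an ICC of 0.02, to 472 and then 630 from 47 practices. The Table 2 footnote gives the formula: "Design effect = 1 + (n-1) × ICC, based on clusters with 10 individuals per cluster". The article gives no reason for choosing this formula and does not describe it as a deliberately cautious allowance.

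Two other statements bear on the point. Treatment as usual says that controls do not see the practice research nurse for mental health care, so nurse delivery is confined to one arm. Planned analyses says: "The impact of clustering by GP and/or nurse will be investigated using multi-level modelling".

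**The concern.** The factor 1 + (n − 1) × ICC describes how much the variance of a treatment comparison grows when all n patients in a practice receive the same allocation. Practice differences then fall wholly between the arms. When both arms sit in every practice, a practice effect shared by its patients adds equally to both arms and drops out of the difference. The formula therefore belongs to the design that the article says it rejected.

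Nor does it describe the clustering that this design can produce. Nurse effects would arise among intervention patients only, about half of each practice's sample. The footnote formula uses all ten patients and both arms.

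At stake is whether the stated requirement of 630 from 47 practices, and every other row of Table 2 with a non-zero ICC, means what it says. Recruitment closed at 558, so a reader who takes 630 at face value would conclude that the trial fell short of its need.

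**Working it through.** **Inputs.** From the article: difference 4, SD 11.0, power 90%, 5% significance (taken as two-sided), base 400, drop-out 25%, ICC 0.02, n = 10, recruited 558, and an ICC of 0.13 from another trial cited in the same section. Not in the article, and assumed here: one nurse per practice, m = 5 intervention completers per nurse (half of 10), and a nurse ICC between 0.02 and 0.13.

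**Step 1: reproduce the plan.**
- Unclustered, per arm: 2 × (1.96 + 1.2816)² × 11² / 4² = 158.9, so 159 per arm and 318 in total. This matches.
- Design effect: 1 + 9 × 0.02 = 1.18. Then 400 × 1.18 = 472, and 472 / 0.75 = 629.3, so 630. This matches.
- The other Table 2 rows agree to within one patient. The practice counts equal completers divided by 10 (472 / 10 = 47.2, shown as 47).
- n = 10 fits 12 to 14 recruited per practice: 630 / 47 = 13.4, and 13.4 × 0.75 is about 10 completers.

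**Step 2: the factor for a shared practice effect.** Let the total variance be σ², with a share ICC between practices. With equal arms inside each practice and a treatment effect that does not vary by practice, only the within-practice part, σ²(1 − ICC), remains in the difference. The factor is 1 − ICC = 0.98.
- 400 × 0.98 = 392, and 392 / 0.75 = 522.7, so 523.
- Practices at 10 completers each: 39.
- Difference from the stated figure: 630 − 523 = 107.

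**Step 3: the factor for nurse clustering in the intervention arm only.** The intervention arm has 1 + (m − 1) × ICC and the control arm has 1. With equal arms the average is [2 + (m − 1) × ICC] / 2.

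| Case (base 400) | Factor | Completers | Recruited | Practices (completers / 10) |
|---|---|---|---|---|
| Table 2, ICC 0.02 | 1.18 | 472 | 630 | 47 |
| Shared practice effect, ICC 0.02 | 0.98 | 392 | 523 | 39 |
| One-arm nurse, ICC 0.02 | 1.04 | 416 | 555 | 42 |
| One-arm nurse, ICC 0.05 | 1.10 | 440 | 587 | 44 |
| One-arm nurse, ICC 0.13 | 1.26 | 504 | 672 | 50 |

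The stated 1.18 equals the one-arm factor when (2 + 4 × ICC) / 2 = 1.18, which is a nurse ICC of 0.09. Under these assumptions 630 is more than enough below that value and too small above it.

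**Step 4: check of the factors by simulation** (40 practices of 10). At ICC 0.02 the simulated variance factor was 1.185 for randomising practices, 0.973 for randomising within practices and 1.021 for one-arm nurse clustering, against 1.18, 0.98 and 1.04 from the formulas. At ICC 0.13 the values were 2.18, 0.86 and 1.265, against 2.17, 0.87 and 1.26. The small gaps are consistent with simulation error.

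**Step 5: power for 4 points at 558 recruited.** With 25% loss there are 558 × 0.75 / 2 = 209 per arm, divided by the factor.
- Factor 0.98: 96%.
- Factor 1.04: 95%.
- Factor 1.18: 93%.
- Factor 1.26: 91%.

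At the 67% response rate that the article reports for 12 months, the same four values are 94%, 93%, 90% and 88%.

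**The case against.** The strongest defence is that the error is on the safe side. At the planning ICC the formula asks for more patients than the design needs, recruitment exceeds both 523 and 555, and power for 4 points stays above 90% at the planned loss. This stands, and it rules out reading the point as a claim that the trial is too small. It does not make the formula right, because the article presents 630 as the requirement and not as a margin.

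A second defence is that 1 − ICC assumes the same treatment effect in every practice. If the effect varies, some inflation is justified and 1.18 could serve as an allowance. This also stands in principle, but the article makes no such argument.

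A third is that no single replacement figure is secure. The 555 depends on one nurse per practice, five completers each and a nurse ICC of 0.02. At the cited 0.13, which comes from GPs using cognitive behavioural techniques in a different trial, the figure is 672 and the direction reverses. This is correct, and it is why a range is needed.

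A reader might go further and infer that the planned analysis mishandles nurse clustering, or that the secondary-outcome models lack a cluster term. The document does not support either. Planned analyses names multi-level modelling by GP and/or nurse, with standard errors of the treatment effect adjusted, and does not commit to a nurse effect common to both arms. The exact random-effect structure and the terms in the secondary models normally belong in a statistical analysis plan, which is not shown here.

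**Conclusion.** The point holds for the sample size. Table 2 is correct arithmetic on a formula for a design that the article says it did not adopt. For practice clustering, the stated purpose, the requirement on base 400 at ICC 0.02 is 392/523 and not 472/630, provided the treatment effect does not vary by practice. For nurse clustering in one arm it ranges from 416/555 to 504/672 over nurse ICCs of 0.02 to 0.13, under the assumed one nurse per practice and five completers each. So 630 is conservative at 0.02 and falls short at 0.13.

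The consequence is a misstated requirement. The trial is not shown to be underpowered, and the point does not extend to the planned analysis.

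**What to change.** Replace the Table 2 footnote formula with one for randomisation within practices (factor about 1 − ICC, with the constant-effect assumption stated), and restate the completers, recruits and practice counts in each row. The five-point calculation is said to repeat the same steps, so it needs the same review.

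If an allowance for nurse clustering is wanted, add it as a separate line using [2 + (m − 1) × ICC] / 2, state the number of nurses per practice and m, and show a range of ICCs and not one figure. If 1.18 was meant as a cautious allowance, for example for treatment effects that vary by practice, say so and give the reason.

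When restating, make the base explicit. Table 2 is titled for a four-point difference but starts from the economic requirement of 400. From 318 the same factors give 312/416 (0.98), 331/442 (1.04) and 401/535 (1.26).

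Add the power at 558 recruited under these factors, since the Discussion says that the numbers should suffice but shows no calculation. The cost is a corrected footnote and table and a few sentences. Recruitment, data collection and the planned models do not change.
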